#### Procedures

From the IH data in the 13th year, we will randomly select 400 IH COPD patients who used the hospital in the subsequent year and automatically explain the prediction results of the best IH model built in Aim 4. We will use patients outside of UWM to help ensure no care manager is aware of any of those patients’ outcome in the subsequent year. We will show every care manager a different subset of 40 patients and proceed in 3 steps:

Step 1: For every patient, we will present the historical de-identified patient attributes and the prediction result to the care manager and ask him/her to record the enrollment decision and interventions, if any, that he/she plans to use on the patient. For the historical patient attributes, we will show the static attributes’ values at the top, followed by the longitudinal attributes’ values in reverse chronological order. No care manager will see any automatic explanation in this step.Step 2: For every patient, we will present the automatic explanations and their linked interventions to the care manager and survey him/her using both semistructured and open-ended questions. The automatic explanations will appear as a list of association rules. Below each rule is the list of interventions linked to the rule. The questions will include whether these explanations would change the enrollment decision for the patient, whether he/she believes they would improve care plan quality, their usefulness on a 1 to 7 scale with anchors of not at all/very useful, and their perceived trustworthiness on a 1 to 7 scale with anchors of not at all/completely. Our questionnaire will embrace a text field for writing comments.Step 3: We will use the standard Technology Acceptance Model (TAM) satisfaction questionnaire [107] to survey the care manager about the automatic explanations. A technology is unimportant unless people will accept and use it. Developed based on multiple well-accepted behavioral theories, TAM is the most widely adopted model of people’s acceptance and usage of a technology. The TAM satisfaction questionnaire will measure the perceived usefulness and the perceived ease of use of automatic explanations. Perceived usefulness is known to link strongly to future usage intentions and to actual function usage [108,109]. Multiple studies have demonstrated the validity and reliability of the TAM satisfaction questionnaire [110,111].

#### Analysis

We will adopt the inductive approach described in Patton et al [106,112] to conduct qualitative analysis. Care managers’ textual comments will be put into ATLAS.ti qualitative analysis software [113]. In total, 3 people in our research team will independently highlight quotations on prediction results and automatic explanations for all records. Quotations will be examined, classified into precodes, and merged into categories via discussion and negotiated consensus in several iterations. We will find general themes via synthesis of categories. The quantitative analyses will include giving descriptive statistics for every quantitative outcome measure. We will test the hypothesis that for the patients who will use the hospital in the next year, giving actionable information will improve the perceived care plan quality. Our hypothesis is as follows:

Null hypothesis: For the patients who will use the hospital in the next year, the care manager does not believe that showing the automatic explanations and their linked interventions would improve care plan quality.Alternative hypothesis: For the patients who will use the hospital in the next year, the care manager believes that showing the automatic explanations and their linked interventions would improve care plan quality

We will fit a random effect logistic model to account for correlation among the outcomes of the same care manager on whether the perceived care plan quality is improved.

#### Justification of the Sample Size

Assuming a moderate intra-class correlation of 0.1 within the same care manager on the outcome of whether the perceived care plan quality is improved, a sample size of 40 instances per care manager for 10 care managers is equivalent to totally 82 independent instances after adjusting for the clustering effect. At a 2-sided significance level of 0.05, we will have 80% power to identify a 9.7% increase in the odds of improving the perceived care plan quality with actionable information. A similar conclusion holds if the actual correlation differs somewhat from the assumed one.

If giving actionable information has no significant impact on the perceived care plan quality on the whole group of COPD patients, we will do subanalyses to find those patient subgroups on which significant impact occurs.

### Experiment 2

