#### Justification of the Sample Size

Assuming a moderate intra-class correlation of 0.1 within the same care manager and within the same patient examined by 2 care managers on the enrollment decision outcome, a sample size of 40 instances per care manager for 10 care managers is equivalent to totally 74 independent instances after adjusting for the clustering effect. At a 2-sided significance level of 0.05, we will have 80% power to identify a 9.7% boost in the intervention group in the odds that a care manager decides to enroll the patient in care management. A similar conclusion holds if the actual correlations differ somewhat from the assumed ones.

As mentioned right before Aim 1, the above discussion focuses on COPD. Whenever we mention COPD, the same applies to asthma and will be developed and tested on asthma also in Aims 1 to 5.

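### Aim 5 claims 80% power for a 9.7% increase in odds, but the stated effective sample sizes give about 5 to 7%, and Experiment 1's effect needs a stated reference value.

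*Protocol article*

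**What the plan says.** Both sample size justifications under Aim 5 of the protocol article start from ten care managers reviewing 40 patients each, 400 reviews in all.

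- **Experiment 1.** "Assuming a moderate intra-class correlation of 0.1 within the same care manager on the outcome", the article says that "40 instances per care manager for 10 care managers is equivalent to totally 82 independent instances after adjusting for the clustering effect". Its claim, for a two-sided test at 0.05, reads: "we will have 80% power to identify a 9.7% increase in the odds of improving the perceived care plan quality with actionable information".
- **Experiment 2.** With an "intra-class correlation of 0.1 within the same care manager and within the same patient examined by 2 care managers", it says that "40 instances per care manager for 10 care managers is equivalent to totally 74 independent instances after adjusting for the clustering effect". Its claim, for the same kind of test, reads: "we will have 80% power to identify a 9.7% boost in the intervention group in the odds that a care manager decides to enroll".

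Neither paragraph gives a baseline proportion. Both add that the conclusion is much the same if the correlations differ somewhat from 0.1.

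In Experiment 1 (Procedures), Step 1 records the enrollment decision and planned interventions without explanations. Step 2 shows the explanations and asks the manager "whether he/she believes they would improve care plan quality". The Analysis section fits a random effect logistic model to that answer and names no reference proportion in the null hypothesis.

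**The concern.** Fewer than 100 effective yes/no observations cannot resolve a shift of about two percentage points. The same 9.7% is attached to a single-condition design with 82 effective instances and to a two-group design with 74, which by itself suggests that the figure was not derived separately for each.

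The wording for Experiment 1 has a second problem. It speaks of an increase in odds with actionable information, but the outcome is collected only after that information has been shown, so there are no corresponding odds without it.

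Aim 5 is presented as preparation for clinical deployment. As printed, its two tests appear sensitive to very small effects when they can detect only large ones. A non-significant Experiment 1 also leads to a search for patient subgroups in which the effect is significant, so its real sensitivity matters for how that step is read.

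**Working it through.** **Inputs from the article:** 10 managers, 40 reviews each, intra-class correlation 0.1 (within manager; in Experiment 2 also within patient), two-sided alpha 0.05, odds ratio 1.097, five managers per group in Experiment 2. **Assumption:** the baseline is not given, so 0.05 to 0.90 is used.

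**1. The plan's effective sizes.**
- Experiment 1: 400 / (1 + 39 × 0.1) = 400 / 4.9 = 81.6, reported as 82.
- Experiment 2: 400 / (4.9 × 1.1) = 74.2, reported as 74, or 37 per group.

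Both reproduce.

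**2. Power for Experiment 1**, one-sample test of a proportion, n = 82:

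power = Φ[(d − 1.96·SE0)/SE1] + Φ[(−d − 1.96·SE0)/SE1], with d = p1 − p0, SE0 = √(p0(1−p0)/n), SE1 = √(p1(1−p1)/n).

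At p0 = 0.50, p1 = 1.097/2.097 = 0.523, d = 0.0231 and SE0 ≈ SE1 ≈ 0.0552. Power = Φ(−1.54) + Φ(−2.38) = 0.061 + 0.009 = 0.070.

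**3. Power for Experiment 2**, pooled two-proportion test, 37 per group: the standard error of the difference is about 0.116. Power = Φ(−1.76) + Φ(−2.16) = 0.039 + 0.015 = 0.054.

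**4. Over the baseline range:**

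| Baseline | Exp. 1, n = 82 | Exp. 2, 37 v 37 |
|---|---|---|
| 0.05 | 6.4% | 5.1% |
| 0.10 | 6.7% | 5.2% |
| 0.30 | 7.2% | 5.4% |
| 0.50 | 7.0% | 5.4% |
| 0.70 | 6.2% | 5.4% |
| 0.90 | 4.8% | 5.2% |

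These figures count rejections in either direction. With all 400 reviews treated as independent, the maximum is about 15% (one sample of 400) and 7.5% (200 v 200). From a 50% baseline, 80% power for an odds ratio of 1.097 needs about 3,670 independent instances in one sample, or about 7,330 per group.

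**5. Reading 9.7 as percentage points.**
- Experiment 1, n = 82: 90% at baseline 0.05, 82% at 0.08, 79% at 0.09, 77% at 0.10, 42% at 0.50, 62% at 0.80, 79% at 0.85, 95% at 0.88.
- Experiment 2, 37 per group: 13% at 0.50, 21% at 0.10 and at 0.80, 47% at 0.90, and no more than about 49% anywhere. With about 42 per group (step 6) the ceiling is about 53%.

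**6. Effective size for the between-group contrast in Experiment 2.** Each patient is seen once in each group. Positive within-patient correlation therefore subtracts from the variance of the difference:

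Var(difference) = (2σ²/200) × (1 + 39 × 0.1 − 0.1) = (2σ²/200) × 4.8.

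This gives 200 / 4.8 = 41.7 effective instances per group, against the article's 37.

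**7. Effects detectable with 80% power, assuming 50% as null or baseline.**
- Experiment 1: 65% (OR 1.9) by the normal approximation; about 66 to 67% (OR 2.0 to 2.1) with t on 9 df for ten managers.
- Experiment 2, about 42 per group: 79% (OR 3.8) normal; about 81 to 83% (OR 4.4 to 4.9) with t on 8 df.
- Experiment 2, 37 per group: about 81% (OR 4.1) normal; up to about 85% with t on 8 df.

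**The case against.** The best defence is a slip of units: 9.7 was meant as percentage points. For Experiment 1 this is possible, since power is near 80% at a baseline of about 0.08 to 0.09 or about 0.85, and higher beyond those values. But both paragraphs say odds, neither gives such a baseline, and no baseline rescues Experiment 2.

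A reader might infer that Experiment 1 has no valid test because it lacks a comparator. The documents do not support that. The question put to the manager is itself comparative, so testing the intercept of a random effect logistic model for a yes/no judgement is coherent. The exact null value may also stand in a fuller protocol or analysis plan. What remains is narrower: the sample size paragraph describes an increase in odds that this single-condition outcome cannot yield, and gives no reference value.

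A reader might also infer that a null result would be reported as no effect. The article does not say so; its stated response for Experiment 1 is subgroup analyses.

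Finally, Aim 5 is one of five aims, a survey in a test setting on de-identified records. That limits the consequences but does not make the power statement correct.

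**Conclusion.** The 80% power claims do not hold as written. For an odds ratio of 1.097, power is about 5 to 7% in Experiment 1 and about 5% in Experiment 2, close to the type I error rate. This does not depend on the assumed baseline (0.05 to 0.90), and changing the correlation does not help, since the claims fail even at zero correlation. The arithmetic behind 82 and 74 reproduces, but the extra divisor of 1.1 that produces 74 runs the wrong way for the between-group contrast. Correcting it helps Experiment 2 only slightly and leaves its power at about 5 to 6%.

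The detectable proportions in the working are illustrations: they rest on a 50% baseline or null that the article does not give. The comparator issue is a mismatch between the stated effect and the outcome, to be settled by restating the effect; it does not invalidate Experiment 1.

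**What to change.** - **Experiment 1:** restate the effect as the proportion of reviews in which the manager judges that care plan quality would improve, tested against a stated reference value. Give the detectable proportion for that value. With 50% as reference this would be about 65 to 67% (OR about 1.9 to 2.1).
- **Experiment 2:** state a baseline enrollment proportion and give the detectable proportion in the intervention group. From 50% this would be about 79 to 83% (OR about 3.8 to 4.9) with about 42 effective instances per group, or about 81 to 85% if 37 is kept. Explain how the within-patient correlation enters the calculation.
- **Both:** allow for the small number of managers, for example with t on 9 and 8 df, and remove or recompute the claim that the conclusion is robust to other correlations. Apply the same correction wherever these figures are carried over to physicians or to asthma.

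The cost is two rewritten paragraphs, one reference value and one baseline. No participants are added; the stated figures only become less favourable.

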#### Procedures

We will randomly partition the 10 care managers into 2 disjoint groups: the intervention group and the control group. Each group has 5 care managers. From the IH data in the 13th year, we will randomly select 200 IH COPD patients who used the hospital in the subsequent year and whose data are unused in Experiment 1 and automatically explain the prediction results of the best IH model built in Aim 4. For each group, we will show every care manager in the group a different subset of 40 patients. With random assignment, each patient is shown to 2 care managers, one in the intervention group and the other in the control group. In the control group, for every patient, we will show the care manager the historical de-identified patient attributes and the prediction result but no automatic explanation. In the intervention group, for every patient, we will show the care manager the historical de-identified patient attributes, the prediction result, the automatic explanations, and their linked interventions. In both groups, we will ask the care managers to record their enrollment decisions.

#### Analysis

We will test the hypothesis that for a patient who will use the hospital in the next year, giving actionable information will increase the likelihood that a care manager decides to enroll the patient in care management. Our hypothesis is as follows:

Null hypothesis: For a patient who will use the hospital in the next year, the likelihood that a care manager in the intervention group decides to enroll the patient in care management is the same as that in the control group.Alternative hypothesis: For a patient who will use the hospital in the next year, the likelihood that a care manager in the intervention group decides to enroll the patient in care management is higher than that in the control group.

We will fit a random effect logistic model to compare care managers’ enrollment decision outcomes between the intervention group and the control group, while accounting for correlation among the enrollment decision outcomes of the same care manager and correlation between the enrollment decision outcomes of the same patient examined by 2 care managers.

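### Experiment 2 randomises only 10 care managers (5 v 5), so an uncorrected large-sample test of the group effect would run at about 1.5 to 2 times its nominal 5% level

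*Protocol article*

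**What the plan says.** The Experiment 2 Procedures section sets the randomised unit: "We will randomly partition the 10 care managers into 2 disjoint groups: the intervention group and the control group". It adds "Each group has 5 care managers" and says that within a group "we will show every care manager in the group a different subset of 40 patients". The 200 patients are crossed with group: "each patient is shown to 2 care managers, one in the intervention group and the other in the control group". This gives 400 decisions.

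The Analysis section plans a random-effect logistic model to compare the decisions "between the intervention group and the control group, while accounting for correlation among the enrollment decision outcomes of the same care manager", and it allows for correlation within patient as well. No test statistic, reference distribution or degrees of freedom is named.

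The Justification of the Sample Size section starts from "Assuming a moderate intra-class correlation of 0.1 within the same care manager and within the same patient examined by 2 care managers". It converts the 400 decisions to 74 independent instances and states power at a two-sided 0.05 level.

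The introduction to Aim 5 says that the evaluation with 10 physicians is similar. Experiment 1 uses a related model for a single group of 10 care managers: "We will fit a random effect logistic model to account for correlation among the outcomes of the same care manager".

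**The concern.** Each patient is rated once in each group, so differences between patients largely cancel out of the group comparison. Differences between care managers do not. However many patients each manager rates, the comparison rests on 10 manager-level results, five on each side.

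A random effect for care manager puts the right variance component in the model, but that component still has to be estimated from 10 people. A Wald z or likelihood-ratio test with its usual large-sample reference treats the estimate as if it were precise, and so rejects a true null too often. Counting 74 independent instances has the same weakness: it adjusts the amount of information for clustering but not the degrees of freedom.

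Aim 5 is the only aim that tests the explanations on clinicians, and the article calls it an essential preparatory step before clinical deployment. A false finding that explanations raise enrolment would therefore carry weight.

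**Working it through.** **Inputs from the article.** 10 care managers, 5 v 5; 40 patients per manager; 200 patients, each rated once per group; intra-class correlation (ICC) 0.1 within manager and 0.1 within patient; two-sided level 0.05. The enrolment rate is not given, so it is assumed and varied below.

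**1. The article's own figure.** The manager design effect is 1 + 39 × 0.1 = 4.9, and the patient design effect is 1 + 1 × 0.1 = 1.1. Then 400/(4.9 × 1.1) = 400/5.39 = 74.2, which reproduces 74.

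**2. Degrees of freedom.** Taken as 74 independent instances in two groups, the comparison has 72 df and a critical value of 1.99. The randomised units give 10 − 2 = 8 df and a critical value of 2.306.

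**3. Closed form on the 10 manager means.** Under the null, the group difference over its standard error follows t on 8 df.
- z test with the unbiased between-manager variance: P(|t₈| > 1.96) = 8.6%.
- Wald z with the maximum-likelihood variance (divisor 10 in place of 8): the effective cut-off is 1.96 × √(8/10) = 1.753, and P(|t₈| > 1.753) = 11.8%.
- Likelihood-ratio test: it rejects when 10 × ln(1 + t²/8) > 3.841, so |t| > √(8 × (e^0.3841 − 1)) = 1.936, and P(|t₈| > 1.936) = 8.9%.

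**4. Simulation of the planned model under the null.** Crossed random effects for manager and patient in both the data and the fit, ICCs on the latent logistic scale, patient ICC 0.1, Laplace maximum likelihood, 4,000 runs per row:

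| Enrolment rate | Manager ICC | Wald z | Likelihood ratio | Wald statistic on t, 8 df | t test on 10 manager rates |
|---|---|---|---|---|---|
| 0.5 | 0.1 | 9.9% | 7.8% | 6.0% | 4.2% |
| 0.3 | 0.1 | 10.6% | 7.8% | 6.1% | 4.2% |
| 0.5 | 0.05 | 10.1% | 7.7% | 6.1% | 4.3% |
| 0.5 | 0.2 | 10.0% | 7.7% | 5.9% | 4.2% |

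A separate run of 3,015 fits with lme4 glmer (rate 0.5, both ICCs 0.1) gave Wald z 334/3015 = 11.1% and likelihood ratio 263/3015 = 8.7%.

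**5. Managers-only check.** Beta-binomial data, 100,000 runs for each combination of enrolment rate 0.2 to 0.7 and ICC 0.05 to 0.2. The z test with unbiased variance gave 7.9% to 8.9%, the z test with maximum-likelihood variance 11.3% to 12.0%, and the t test on 8 df 4.5% to 5.4%.

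**6. Permutation test.** There are C(10,5) = 252 possible 5 v 5 partitions. The smallest attainable two-sided p is 2/252 = 0.008, and the largest attainable level not above 5% is 12/252 = 4.8%. Significance is within reach and the level is held by construction.

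**7. Experiment 1, closed form only.** With one group of 10 managers there are 9 df. P(|t₉| > 1.96) = 8.2%. With the maximum-likelihood variance the cut-off is 1.96 × √(9/10) = 1.859, and P(|t₉| > 1.859) = 9.6%.

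**The case against.** The strongest reply is that the article contains no wrong statement here. It names a suitable model with the right clustering and leaves the test statistic open. The same model referred to t on 8 df gives about 6% error and complies fully with the Analysis section. A condensed article may leave the reference distribution to a full protocol or analysis plan that is not shown. This stands to the extent that the inflation is conditional on an uncorrected test. It does not dispose of the point, because the article shows its reasoning in the sample-size paragraph: 74 independent instances at a two-sided 0.05 level is a large-sample argument that 5 v 5 randomised managers do not support. It makes the model's default test the natural reading.

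Three stronger readings are tempting and are not supported.
- A reader might infer that any standard test doubles the error rate. Only Wald z does so; the likelihood-ratio test is inflated about 1.5 to 1.8 times.
- A reader might expect the inflation to grow with the manager ICC. With both random effects fitted, it is flat from 0.05 to 0.2.
- A reader might carry the Experiment 2 figures over to Experiment 1. That is a single-group test with no randomised contrast, checked here only by closed form.

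It can also be said that a t test on ten rates sets aside the patient pairing and is slightly conservative (4.2% to 4.3% in the crossed design). That is fair, and is a reason to keep the model for estimation and to offer t on 8 df as the least disruptive choice. Finally, Aim 5 is a test-setting study with randomised trials deferred to later work, which limits the consequence of an error.

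**Conclusion.** The point holds in conditional form. The group effect in Experiment 2 has 8 between-manager degrees of freedom, and the sample-size reasoning does not reflect this. If the usual uncorrected test is used, a nominal 5% two-sided test rejects a true null about 10% to 11% of the time with Wald z and about 8% to 9% with the likelihood ratio, so about 1.5 to 2 times as often as stated.

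These figures rest on the article's 5 v 5 allocation, 40 patients per manager and patient ICC of 0.1. The crossed-model simulations assumed enrolment rates of 0.3 and 0.5 and manager ICCs of 0.05 to 0.2; within those ranges the result barely moves. The 10-physician repeat inherits the problem if it follows the same design. Experiment 1 probably needs an analogous correction, with a closed-form error of about 8% to 10%, but this was not simulated. The correction should be made; it does not invalidate the design.

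**What to change.** In the Experiment 2 Analysis section, keep the random-effect logistic model with care-manager and patient effects as the source of the odds ratio, and name a small-sample basis for the test. Either of these would do:
- refer the model's group-effect Wald statistic to t on 8 df (critical value 2.306; about 6% error); or
- test the 10 care-manager enrolment rates with a t test on 8 df or a permutation test over the 252 partitions (about 4% to 5% error).

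Choose one before the data are seen, and apply the same rule to the 10-physician repeat. For Experiment 1, consider a reference on 9 df (critical value 2.262) after confirming it by simulation.

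The cost is a change of wording. Recruitment, procedures and data are untouched. Nominal power will be slightly lower, because part of the uncorrected test's apparent power comes from its inflated error rate.
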